#### Audit/records of communications (to health professionals and families)

Communication between the PĒPI ARC Hub, families, and health professionals will be captured via notifications to the PĒPI ARC email (Objective 4, Table 4). These will be filed in the inbox according to themes throughout the duration of the study and then reviewed and analysed after study completion.

#### Questionnaires

Questionnaires will provide quantitative and qualitative information. Questions were developed based on the theoretical framework of acceptability to evaluate the following constructs of acceptability: affective attitude, burden, ethicality, intervention coherence, opportunity costs, perceived effectiveness, and self-efficacy (18).

Families will be sent a link of the anonymous questionnaire within 2 weeks of attending the PĒPI ARC clinic or at 5–6 months CGA if their infant is followed up out in their local region. Display logic is embedded within the questionnaire to adjust the line of questions relating to in-person vs. virtual Hub attendance. All families will be asked to reflect on their experiences of communication, resources, and support (Objective 3, Table 4).

Health professionals attending a PĒPI ARC clinic and who are not members of the regular PĒPI ARC team will be sent a survey within 2 weeks of the clinic appointment. Other health professionals not part of the PĒPI ARC team who have engaged with the Hub (through email audit trail review and being identified as being a primary person involved in the care of an infant) will be sent a survey invitation between 6 and 12 months of PĒPI ARC operating (Objective 3, Table 4).

The members of the PĒPI ARC team will complete a specific team questionnaire focused on the acceptability of PĒPI ARC 3 months after clinic commencement. The data from the team questionnaire will be analysed in real time (i.e., within 4 weeks of capture) to allow for any changes to the study conduct if indicated. The questionnaire will be repeated at the study endpoint to reassess for potential changes for service improvements (Objective 3, Table 4).

Full analysis of all questionnaire data will occur at the end of the study period.

#### Semi-structured interviews

Semi-structured interviews will seek to capture the acceptability of PĒPI ARC (18) in addition to the experiences around communication of the diagnostic outcome, information sharing, and resources and emotional supports provided (Objective 6, Table 4). Questions will target the experiences of implementing the CPCN Recommendations within local and regional settings for health professionals and support provided by the PĒPI ARC team. A qualitative descriptive approach will be used to understand the experiences of whānau and health professionals in the unique PĒPI ARC Hub context of healthcare delivery. All semi-structured interviews will be offered to take place in a mode of the participant's preference (face to face at the site of the clinic Hub or via videoconference). All interviews will be led by a researcher who is experienced in qualitative interviewing and who has not been in direct contact with the participant as part of the PĒPI ARC Hub and will be audio recorded for transcription.

Initially, all families who have not opted out of being interviewed will be sent an email invitation once their infant is over the age of 6 months CGA. A staged review of recruitment of interviewees will occur after 6 months to ensure that a cross section of infants has been captured, i.e., regional and local, ethnic diversity especially representation of Māori and Pasifika, term and preterm infants, and with/without likely diagnosis of CP. If indicated, purposive sampling will then be used to target underrepresented participant groups.

Health professionals who have had interactions (i.e., received PĒPI ARC clinic letters and GMA reports, email enquiries, and education sessions) with PĒPI ARC over the first 12 months, but are not part of the PĒPI ARC team, will be invited to take part in an interview via email. They will be identified from attendance at in-person clinics or Zoom encounters, audit trail of emails, and PĒPI ARC education/training sessions.

Interviews will be conducted until a saturation of experiences has been reached (i.e., no new experiences are introduced within the interviews) or a wide range of participants and experiences have been collected to ensure “information power” (27). The diversity of participants will be reviewed monthly thereafter, and targeted recruitment may be used. Qualitative thematic analysis will occur separately for family and health professional data but will occur concurrently to help determine any crossover of themes following the methods outlined by Braun and Clarke (28). The themes will be interpreted and discussed and help inform the quantitative data.

## Ethics and dissemination

This study was approved by the NZ Health and Disability Ethics Committee (HDEC: 2022 FULL 13434) and is registered on the Australian NZ Clinical Trials Registry (ACTRN12623000600640). Any modifications to the study protocol will be submitted as an amendment to the ethics committee, and an update will be provided to the ACTRN registration. Informed written consent will be obtained from participants, and data will be de-identified for reporting. Health professionals completing anonymous questionnaires will indicate their consent by questionnaire completion, and those completing interviews will provide written consent. The results of the study will be published and disseminated [co-authored by investigators meeting the authorship criteria of the International Committee of Medical Journal Editors (ICMJE)] in conference abstracts and presentations, peer-reviewed articles in scientific journals, the PĒPI ARC community, organisation newsletters, and media releases. A de-identified dataset may be made available upon reasonable request but may be restricted by ethical limitations.

## Discussion

This paper details the protocol for a feasibility study to ascertain if a multidisciplinary regional Hub, namely, PĒPI ARC, can support the equitable implementation of the NZ CPCN *Best Practice Recommendations for Early Detection of CP, Intervention, and Monitoring* for infants with newborn detectable risks. Feasibility will be assessed for acceptability and demand among families and health professionals and for efficacy in relation to reducing the age of CP diagnosis and improving experiences around communication and information sharing between families and health professionals.

The study is limited to only infants with newborn detectable risk factors for CP who are admitted to the Wellington NICU and who either live in Wellington or in one of its referral regions. As there is no control group, our “usual care” infants with the same risk factors who decline to participate will not be followed and therefore cannot be compared to the PĒPI ARC participants. Economic analysis of the effectiveness of PĒPI ARC for families and the health system will not be conducted.

The study has many strengths. One is the delivery of the Hub using two parts: an MDT face-to-face clinic and a regional virtual approach provides an opportunity to decrease inequitable access to care for local and regional infants and families. Some regional centres may not have the experienced staff to deliver the CPCN Recommendations, and the Hub will support and educate clinicians to ensure regional centres can, over time, deliver the recommended assessments and follow-up. The inclusion of qualitative feedback from both families and health professionals will provide depth of context to our findings.

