### Primary objective

1.**Implementation:** to determine to what extent the CPCN Recommendations for early CP diagnosis can be equitably implemented for infants with newborn detectable risks who are admitted to a level 3 NICU (independent of place of residence and ethnicity) and if the fidelity of the CPCN Recommendations can be maintained

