### Hypotheses

**H1**: Equivalent levels of infants who meet the criteria will undergo assessments with CP-specific diagnostic tools outlined in the CPCN Recommendations, independent of region of residence or ethnicity.

**H2**: Whānau and health professionals will find the PĒPI ARC Hub model of care acceptable (over the acceptability constructs).

**H3**: The demand will be high with infants who meet the criteria choosing to enroll in the PĒPI ARC study over standard care.

**H4**: More than 34% of infants with CP will be diagnosed before 12 months of corrected gestation age (CGA) and >17% before the age of 6 months CGA.

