#### Infants and parents/caregivers

Infants must meet the following eligibility criteria:
i.admitted to the NICU at Wellington Regional Hospital within the study period,ii.have a discharge address located within the Wellington region or within one of the referral regions of the Wellington NICU, andiii.and meet the criteria of the CPCN Recommendations for newborn detectable risks for CP (Table 1).Infants will be excluded if they are born with a life-limiting condition and not expected to survive past the first year of life or if the family is expected to move out of the catchment area before the infant is 3 months CGA.

Infants and their parents/caregivers will be invited to participate in the study by a member of the PĒPI ARC research team (not directly involved in providing healthcare for the infant in the NICU). Recruitment can occur at any point during the NICU admission prior to discharge. Support from social workers and Whānau Care Services is available to assist with recruitment decision-making, and parents are encouraged to discuss and seek support from their extended family. Families will be advised that they can instead choose the usual care option (see below).

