### Outcome measures and data collection

Feasibility will be assessed by using the outcomes, measures, and data capture summarised in Table 4, from March 2023 to September 2024. Data will be directly entered into REDCap (hosted by the Wellington Hospital and MRINZ infrastructures), which will only be accessed by the members of the research team involved in the data entry and analysis. Due to the scope and minimal risks associated with the study, there is no formal data monitoring committee. Interim data monitoring will be conducted at a 6-month review of survey feedback, and auditing of trial conduct will be completed by the primary investigator and study and clinical coordinators on a fortnightly basis. Quantitative data collection tools, surveys for families, health professionals and the PĒPI ARC MDT team, participant information, consent form, and data management plan are available on Open Science Framework (OSF, DOI: https://doi.org/10.1101/2023.10.31.23297869).

**Table 4 T4:** Summary of outcomes, data capture, and measures/approaches for PĒPI ARC.

Objective	Data capture	Measures/approaches
Implementation		
1. To determine to what extent the early CP detection assessments can be implemented equitably to infants with newborn detectable risks admitted to a level 3 NICU	• Demographic information for infants eligible for the CPCN Recommendations pathway (NICU discharge data) • PĒPI ARC clinic notes and medical records	The proportion of infants completing the neuroimaging, GMA, and HINE (as per CPCN Recommendations), with outcomes grouped and compared by: • Region of residence • Ethnicity (Māori, Pasifika, non- Māori/Pasifika)

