2. To evaluate if the fidelity of the CPCN recommendations can be maintained, including diagnostic assessments completed, communication with families, and related referrals	• Infant medical records/PĒPI ARC clinic notes • Records for assessments • Referral data • Questionnaire—health professionals • Semi-structured interviews with health professionals and families	The total number and proportion of diagnostic tests completed/not completed (i.e., not grouped by region or ethnicity). Of participants with a high risk of CP/CP detected: • The number of participants whose parents were informed of the diagnosis, and the age and acceptability of communication • The timing of therapist review post high-risk CP diagnosis • The timing of referral for surveillance of comorbidities and medical complications as indicated • The number of families receiving information about practical and emotional support
Acceptability		
3. To evaluate the acceptability of the PĒPI ARC Hub model of care by families and health professionals	• Questionnaires—families, health professionals, and the PĒPI ARC team. • Semi-structured interviews with families and health professionals	Data will be interpreted according to those families and health professionals involved in the Hub who were from Wellington compared with other regional centres
Demand		
4. To determine the demand for the PĒPI ARC Hub among families and health professionals	• PĒPI ARC clinic notes/statistics • Infant medical records (virtual Hub) • Communications with the PĒPI ARC team: logged as part of an audit trail. The full audit trail will be reviewed at the end of the study in combination with questionnaire data	Using the number of infants and families approached to take part in PĒPI ARC: • The proportion of families who consent to the study • The proportion of infants who attend the clinic • The proportion of infants who complete regional follow-up appointments with paediatricians/therapists • The proportion of families that chose to use telehealth • The number and profiles of health professionals accessing the Hub for support • The type of support requested by families and health professionals
Limited efficacy		
5. To evaluate if the PĒPI ARC Hub model reduces the age of CP diagnosis	• PĒPI ARC clinic notes • Infant medical records	• The average age when a preliminary high-risk CP or CP diagnosis was made and age (/rate) of CP confirmation

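### H1 covers every eligible infant, but completion is known only for enrolled infants and uptake is not planned by region or ethnicity, so unequal uptake can be hidden from the equity conclusion

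*Protocol article*

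**What the plan says.** The primary objective asks whether the recommendations "can be equitably implemented for infants with newborn detectable risks who are admitted to a level 3 NICU (independent of place of residence and ethnicity"). H1 predicts "Equivalent levels of infants who meet the criteria will undergo assessments with CP-specific diagnostic tools outlined in the CPCN Recommendations", independent of region and ethnicity. Neither sentence is limited to families who enrol.

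Under Participants and recruitment, recruitment must take place before NICU discharge, and families are told that they may have usual care instead. On those who decline, the Discussion says that "infants with the same risk factors who decline to participate will not be followed and therefore cannot be compared to the PĒPI ARC participants".

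In Table 4, the Objective 1 measure is "The proportion of infants completing the neuroimaging, GMA, and HINE (as per CPCN Recommendations), with outcomes grouped and compared by" region of residence and ethnicity. The denominator is given only as infants. The data capture for the same row includes "Demographic information for infants eligible for the CPCN Recommendations pathway (NICU discharge data").

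Uptake appears under Demand as "The proportion of families who consent to the study". The stated base is the infants and families approached, and no grouping is given. The statistical paragraph under Clinic/medical data reports recruitment rates descriptively. It applies a chi-squared or Fisher's exact test, at p < 0.05, to the extent of implementation between regions and ethnicities.

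**The concern.** An infant reaches the Hub in steps: being eligible, being approached, having a consenting family, and completing each assessment. Inequity can arise at any of them. The only step that the plan says it will compare by region and ethnicity is the last. If that comparison is made among enrolled infants, groups with very different uptake can show the same completion.

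Equity is the primary objective, so a finding of equal completion would be read as showing that the pathway was equitably implemented for infants admitted to the NICU. The data would support that only for families who joined. Eligible infants who were never approached would be missing from both the completion measure and the consent measure.

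**Working it through.** **Figure to reproduce.** The article gives no expected consent rate, completion rate or equivalence margin for H1, so there is no planned figure to check. The rates below are assumptions chosen to show the mechanism.

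**Population against data**

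| Element | Population |
|---|---|
| Primary objective and H1 | All infants meeting the criteria |
| Follow-up for completion | Enrolled infants only (Discussion) |
| Objective 1 measure | Denominator not stated |
| Objective 1 demographics | All eligible infants (discharge data) |
| Consent proportion | Families approached, no grouping stated |

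The Objective 1 row also lists medical records as a source. Given the Discussion, these cannot be taken to supply assessments after discharge for infants whose families declined.

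**Formulas.** Let c be the proportion of eligible infants who enrol, and f the completion among those enrolled.

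- Completion among enrolled infants = f.
- Lower bound among eligible infants (no non-enrolled infant assessed) = c × f.
- Upper bound among eligible infants (every non-enrolled infant assessed) = c × f + (1 − c).

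**Illustration 1: two groups, assumed c = 0.85 and 0.60, f = 0.90 in both**

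- Enrolled: 90% v 90%.
- Lower bound: 0.85 × 0.90 = 76.5%; 0.60 × 0.90 = 54%; difference 22.5 points.
- Upper bound: 76.5% + 15% = 91.5%; 54% + 40% = 94%.

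With c = 0.80 v 0.70, the lower bounds are 72% and 63%, a 9-point difference.

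**Illustration 2: the article's own counts.** Up to 120 eligible infants are expected and about 30% live in Wellington, which gives 36 Wellington and 84 regional infants. Consent rates and f = 0.90 are again assumed, with counts rounded to whole infants. P values are from Fisher's exact test.

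| Consent, Wellington v regional | Completed / enrolled | p | Completed / eligible (non-enrolled counted as not assessed) | p |
|---|---|---|---|---|
| 90% v 90% | 29/32 (91%) v 68/76 (89%) | 1.00 | 29/36 (81%) v 68/84 (81%) | 1.00 |
| 90% v 75% | 29/32 (91%) v 57/63 (90%) | 1.00 | 29/36 (81%) v 57/84 (68%) | 0.19 |
| 90% v 60% | 29/32 (91%) v 45/50 (90%) | 1.00 | 29/36 (81%) v 45/84 (54%) | 0.007 |

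In the last row the 4 Wellington and 34 regional infants not enrolled have unknown status. The bounds are 29/36 to 33/36 (81% to 92%) for Wellington and 45/84 to 79/84 (54% to 94%) for the regions. These ranges overlap almost entirely, so the data would not show whether all eligible infants were assessed equally.

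**The case against.** The strongest reply is that the text does not shut uptake out. The Objective 1 denominator is left open, and demographics of all eligible infants are a listed source for that very row. The demand objective names both local and regional families, and H3 is itself worded on infants who meet the criteria. Where the authors mean ungrouped reporting, as for Objective 2, they say so; the consent measure carries no such note. The Discussion sentence explains why there is no control comparison and does not define the set for H1. All of this stands. A reader might infer that the plan fixes the equity comparison to enrolled infants, removes uptake from it and pools consent. The article does not go that far.

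A second reply is that infants who do not enrol cannot be counted as unassessed. This also stands. The usual-care sections describe routine MRI for HIE Grades 2 and 3, therapists in Wellington who may help with GMA and HINE, HINE-trained therapists in every region, and GMA scoring locally or through Wellington for six regional centres. Completion through the study over all eligible infants is thus a lower bound and not the H1 quantity.

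A third reply is that denominators and flow tables belong in an analysis plan that is not shown. That is fair for table layout. It does not resolve the mismatch, because no analysis plan can supply completion for infants who are not followed, and the article itself sets both H1's population and the approached-families base for consent.

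**Conclusion.** The point holds in a limited form. H1 and the primary objective name a population in which completion will be only partly observed, and no listed measure is stated to show uptake by region or ethnicity. An equity comparison made as the text permits can look equal while reach is not: 90% v 90% among enrolled infants beside 76.5% v 54% of eligible infants known to be assessed through the study.

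The size rests wholly on assumed consent and completion rates. The article gives no evidence that uptake will differ, and with equal consent there is no distortion. It would be wrong to conclude that the plan is bound to miss unequal uptake, since the discharge data needed to show it are already to be captured. Nor does the 22.5-point gap measure a difference in infants assessed by any route, which would remain unknown.

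**What to change.** 1. Within the primary equity result, tabulate eligible, approached, consented and assessed numbers (each of neuroimaging, GMA and HINE) by region and by ethnicity. Use eligible infants as the denominator for uptake, and give 95% confidence intervals.
2. State the denominator of the Objective 1 measure.
3. Choose one form of H1. Either limit it to enrolled infants, with equity of uptake reported beside it, or keep all eligible infants and report completion as bounds, from no non-enrolled infant assessed to every one assessed.
4. Word the conclusion to match: completion among participants, and reach among eligible infants, as two separate statements.

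The eligible counts come from the discharge data in Table 4, and the approached and consented counts from the demand measures. Aggregate de-identified counts are enough for infants who do not enrol, and no extra visit or follow-up is needed. The cost is a few more table rows and a headline figure that will be less favourable or wider.

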## Strengths and limitations of the study

•The New Zealand (NZ) best practice recommendations for early detection of cerebral palsy (CP) are based on international guidelines and have been peer reviewed for the Aotearoa NZ context.•Local and regional health professionals have collaborated to inform the PĒPI ARC protocol with the aim to improve access to early CP assessments and early detection rates of CP.•Reduction in health inequities for Māori and Pasifika have been targeted through informed partnerships.•Resource development and planning of PĒPI ARC Hub has been co-designed with families and recognises the ecological context of Aotearoa NZ.•A limitation is that only high-risk infants with “newborn detectable risks” will be included in the study.
